### Sample size

This single-center study will recruit patients for 2 years (24 months) since official opening. The expected accrual is about 20 VLBW infants, either IUGR or non-IUGR. The power calculations below are based on a two-tailed t-test with I-type error α=0.05 and show the power that the 20-patient study will achieve under various differences in CSOR from the ‘baseline’ impact observed under BN. On the basis of previous studies [21] this is expected to be 0.10 (mean of CSOR pre-post prandial difference), while various hypothesis are made about its standard deviation, σ_CSOR_

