## Methods and design

This is a randomized, non-pharmacological, single-center, cross-over study. Duration of the study: 24 months. The study takes place in the Neonatal Intensive Care Unit.

This study aims at recruiting about twenty very low birth weight infants, either IUGR or NON-IUGR.

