#### Statistical analysis

The primary aim of the study is to compare the impact on intestinal perfusion of 2 different nutrition modalities, bolus (BN, Group A) versus a 3-hour nasogastric nutrition (CN, Group B). The impact on intestinal perfusion is defined as the difference between pre- and post-prandial CSOR values measured with NIRS 30 minutes before feeding and at the expected peak after feeding (3 hours in CN and 30 minutes in BN). Pre- and post-prandial CSOR values will be calculated as the mean of 5-minute NIRS evaluations about the intended time-point (e.g. for baseline CSOR measurement, 2.5 minutes before and 2.5 minutes after the 30th minute before start of the randomized feed). Given that the study is a cross-over study, each infant will be evaluated both for CN and BN and the cross-over CSOR difference will be the primary endpoint.

As a secondary analysis, the cross-over difference of CSOR values as well as that of SO2s values (i.e. the splanchnic saturation slope) will be analysed comparing intra-uterine growth (IUGR vs. non-IUGR).

The impact of the 2 nutrition modalities on CSOR will also be studied in a multivariable context, adjusting for factors including the baseline CSOR value, the baseline Doppler flow velocimetry (both measured within the first 72 hours of life) and the intra-uterine growth (IUGR vs. non-IUGR).

Other secondary analyses include:

· Comparison of the time needed to reach full enteral feeding (i.e. days from randomization till enteral intake of 160 mL/Kg/day of formula or human milk) by randomized arm;

· Comparison of growth as measured by weight, length and head circumference by randomized arm. Main comparison will be between measures at randomization and at achievement of full enteral feeding. The growth at 28 days of life will also be compared with the appropriate standard growth curves.

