The primary end-point analysis as well as all secondary analyses regarding randomized patients will be based on the ITT (intention-to-treat) principle. Comparisons of the two arms accounting for deviations from the assigned arm (analyses by “performed treatment”) will also be added to this main analysis. The primary endpoint will be analyzed with a two-tailed matched pairs t-test, after checking of appropriateness of assumptions. In particular, checking will concern the normality assumption, since period effect and cross-over effect appear both very unlikely in this study. Should normality be not adequate, non-parametric test such as the Wilcoxon signed ranks test will be applied [20]. An appropriate generalized linear model will be used to investigate the relationship between the CSOR cross-over difference and the candidate covariates. Should any raw CSOR observations be missing (e.g. NIRS instrument failed to measure or to save measurements), their estimation via imputation or other appropriate methods will be taken into account. The comparison of growth variables by randomized arm will be performed with either the two-tailed t-test or a non-parametric alternative (e.g. Mann–Whitney test), should the normality assumption be not reasonable. The time from randomization till achievement of the full enteral feeding will be analysed with the Kaplan-Meier estimator, in which full enteral feeding as defined in the protocol will be considered as the sole ‘event’, while censoring will occur for withdrawal for any cause. Standard errors will be computed according to Greenwood formula and the log-rank test will be used for univariate comparisons.

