### Sample size: 20 infants

The power calculations in different scenarios show that with 20 patients the study will achieve a good power in presence of a cross-over difference of at least 0.07 (Table 1).

**Table 1 T1:** Impact on CSOR under BN=0.10

**σ**_**CSOR**_	**CSOR cross-over difference**	**Power**
0.10	0.07	84%
0.15	0.10	80%
0.20	0.13	78%

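### The claim of good power for a cross-over difference of 0.07 or more holds only at the smallest of Table 1's three standard deviations, and the SD described in the text is not the one the table uses

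*Protocol article*

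**What the plan says.** The protocol article's Statistical analysis section fixes the endpoint and the test. The effect of a feed is its pre- to post-prandial change in CSOR, and "each infant will be evaluated both for CN and BN and the cross-over CSOR difference will be the primary endpoint". For the test, "The primary endpoint will be analyzed with a two-tailed matched pairs t-test".

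The Sample size section gives the number and the basis of the power figures. "The expected accrual is about 20 VLBW infants, either IUGR or non-IUGR", and the calculations are "based on a two-tailed t-test with I-type error α=0.05". The reference effect is the mean pre-post change under bolus feeding (BN), and the SD is introduced in the same sentence: "this is expected to be 0.10 (mean of CSOR pre-post prandial difference), while various hypothesis are made about its standard deviation".

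Table 1 has three rows for 20 infants:

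| σ_CSOR | Cross-over difference | Stated power |
|---|---|---|
| 0.10 | 0.07 | 84% |
| 0.15 | 0.10 | 80% |
| 0.20 | 0.13 | 78% |

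The sentence that introduces the table says that "with 20 patients the study will achieve a good power in presence of a cross-over difference of at least 0.07". It puts no condition on σ.

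**The concern.** There are two separate problems.

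First, the summary sentence claims more than the table shows. The table pairs 0.07 with the smallest σ only. At the two larger values it moves to differences of 0.10 and 0.13 to keep power near 80%. A reader who takes the sentence at face value will believe that 0.07 is detectable in all three scenarios.

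Second, the text and the table appear to use different standard deviations. As worded, σ_CSOR belongs to one pre-post change, under BN. The power of a matched pairs t-test depends instead on the SD of the within-infant difference between two such changes. The two SDs are linked by the within-infant correlation, which the article does not give.

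What is at stake is how the result is read. If the primary test is not significant, the power statement will be used to judge whether a difference of 0.07 has been reasonably excluded. That judgement depends on which σ applies and on what σ means.

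**Working it through.** **Inputs from the protocol article.** n = 20 and two-sided α = 0.05 (Sample size); matched pairs t-test on the cross-over difference (Statistical analysis); the three pairs of σ and difference d (Table 1).

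**Input not in the article.** The within-infant correlation ρ between the BN and CN pre-post changes. It is varied below as an assumption.

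**Step 1: reproduce Table 1.** Enter σ directly as the SD of the paired difference. The noncentrality is λ = (d/σ)·√20, with df = 19 and critical value 2.093. Power is the probability that a noncentral t(19, λ) falls outside ±2.093.

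| σ | d | λ | Power | Stated |
|---|---|---|---|---|
| 0.10 | 0.07 | 0.700 × 4.472 = 3.13 | 84.4% | 84% |
| 0.15 | 0.10 | 0.667 × 4.472 = 2.98 | 80.7% | 80% |
| 0.20 | 0.13 | 0.650 × 4.472 = 2.91 | 78.7% | 78% |

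The table reproduces to within one percentage point. The other calculations tried do not:
- paired normal approximation: 87.9/84.7/82.8%
- one-sided paired t: 91.5/89.0/87.6%
- two-sample t with 10 per arm: 31.7/29.2/28.0%
- two-sample t with 20 per arm: 57.8/53.8/51.7%

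The table therefore treats σ as the SD of the cross-over difference.

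**Step 2: test the 0.07 sentence on the table's own method.** Hold d at 0.07 and vary σ.

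| σ | λ | Power at d = 0.07 | d giving 80% power |
|---|---|---|---|
| 0.10 | 3.13 | 84% | 0.066 |
| 0.15 | 2.09 | 51% | 0.099 |
| 0.20 | 1.57 | 32% | 0.132 |

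This step needs no assumption about ρ. It gives σ the meaning that reproduces the table.

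**Step 3: read σ as the Sample size text words it.** If each pre-post change has SD σ, the SD of the paired difference is σ·√(2(1−ρ)). The multiplier is 1 exactly when ρ = 0.5, so the table agrees with the text only at that value.

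| Assumed ρ | Multiplier √(2(1−ρ)) | Power, rows 1/2/3 |
|---|---|---|
| 0 | 1.414 | 56/52/50% |
| 0.25 | 1.225 | 68/64/62% |
| 0.5 | 1.000 | 84/81/79% |
| 0.7 | 0.775 | 97/95/94% |

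As an example, row 1 at ρ = 0 has an SD of 0.10 × 1.414 = 0.141 and λ = (0.07/0.141) × 4.472 = 2.21, which gives 56%.

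**The case against.** The strongest reply is that Table 1 is not miscalculated. It matches the planned test once σ is taken as the SD of the cross-over difference, and σ stands beside that difference in the table. The authors may simply have meant that SD, in which case one clause is loosely worded and no tabulated figure changes. This stands. The documents do not establish that the wrong SD was put into the calculation, only that the text describes one SD and the table works with another.

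A reader might also infer that the trial is underpowered. The documents do not support that. They give no correlation, and above 0.5 the power would be higher than stated.

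Nor does the choice of 20 infants rest on these figures. The Sample size section presents 20 as the expected accrual over 24 months at one centre and derives power from it, and the Discussion calls the study explorative. The article gives no attrition rate either, so a power figure for fewer evaluable infants would have no basis in it.

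On the 0.07 sentence, the reply is that it refers to several scenarios and the table follows directly. A careful reader can see that 0.07 goes with σ = 0.10 only. That softens the effect but does not make the sentence true, because it is worded without a condition and fails in two of the three scenarios it summarises.

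**Conclusion.** The concern holds in two limited parts.

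The unconditional claim about 0.07 is wrong as written. On the table's own method it is met at σ = 0.10 and missed by a wide margin at 0.15 and 0.20. This part is firm.

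The meaning of σ_CSOR is inconsistent between the text and the table. If the text is right, the stated power is correct only at a correlation of 0.5. Over assumed correlations from 0 to 0.7, row 1 runs from 56% to 97%, row 2 from 52% to 95% and row 3 from 50% to 94%. The direction of any error is therefore unknown. This part assumes that the two changes have equal SDs, and ρ is an assumed range. If the table is right, only the definition needs correcting.

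Neither part calls into question the number of infants, the endpoint or the test.

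**What to change.** 1. Replace the summary sentence with a conditional one, for example: *With 20 infants the study has about 80% power for a cross-over difference of about 0.07, 0.10 or 0.13 if the SD of that difference is 0.10, 0.15 or 0.20 respectively.*
2. State in the Sample size section and in the heading of Table 1 that σ_CSOR is the SD of the cross-over difference, if that is what was meant.
3. If σ_CSOR is instead the SD of a single pre-post change, give the assumed within-infant correlation and its basis. Restate power over a range on both sides of 0.5, and adapt the sentence in item 1 to match.

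The cost is a change of wording and, under item 3, a recalculated table whose figures may go up or down. No extra infants, procedures or design changes are needed.

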### Sample size: 20 infants

The power calculations in different scenarios show that with 20 patients the study will achieve a good power in presence of a cross-over difference of at least 0.07 (Table 1).

**Table 1 T1:** Impact on CSOR under BN=0.10

**σ**_**CSOR**_	**CSOR cross-over difference**	**Power**
0.10	0.07	84%
0.15	0.10	80%
0.20	0.13	78%

### Data collection

The case report form (CRF) attached to the protocol describes the data needed for each patient (see Additional file 1). A specific database will be set up which will capture the data produced by the NIRS instrument and automatically saved in an exportable file and the demographic and clinical data routinely available in the electronic clinical chart used by the center. Other variables, collected *ad hoc* for this study, will be entered in the same database by the Trial Data Center.

## Discussion

This is an explorative study. Evaluations of intestinal oximetry and superior mesenteric artery blood flow after the feed may help in differentiating how the feeding regimen alters the splanchnic blood flow and oxygenation and if the changes induced by feeding are different in IUGR versus NON IUGR infants.

We postulate that TOI will be altered in the vascular bed when blood flow is decreased; the resultant acidosis in poorly perfused tissues may also further increase the dissociation of oxygen from haemoglobin and increase the portion of reduced haemoglobin detected with NIRS. This condition may be present in IUGR infants and this condition may alter feeding tolerance thus requiring a longer time to achieve full enteral feeding and increasing the episodes of feeding intolerance.

Gut perfusion may depend on the way of administering feeding, bolus or continuous nutrition, so this study may suggest which is the best way to feed VLBW infants.

### Legal and ethical requirements

Direct access to data/original documents.

I/We hereby declare that the experimenter will grant examination, revision of the IRB/IEC, and the inspection by the competent authority through direct access to data/original documents.

### ’Liability

#### Legality of the study

The study will be conducted in conformity with the laws in force.

Protection of the patient’s personal data.

Participants’ personal data and the study results will be treated confidentially according to DL 30/06/2003 n.196.

#### Informed consent

Parents (or people with parental authority) of eligible patients will be informed and provided with details by any of the assigned doctors.

#### Ethics committee approval

The study received approval of the Ethics Committee.

#### Helsinki declaration

The study will be conducted in conformity with principles and regulations of the Helsinki Declaration and its amendments.

#### Quality assurance and quality control

Reference to the guidelines for Clinic Good Practice (CPMP/ICH/135/95).

The Center of Biostatistics for Clinical Epidemiology, University of Milano-Bicocca will analyze the outcomes of the study.

Regulation of the data promulgation.

The final results of the study will be published even in case of non attainment of the goals. The publication will refer to the “CONSORT Statement” [22,23] and will include complete analyses on security. Data of the study shall be published or reproduced upon Trial Steering Committee notice.

## Abbreviations

NEC, Necrotizing enterocolitis; NIRS, Near infrared spectroscopy; MEF, Minimal enteral feeding; EN, Enteral nutrition; NPT, Total parenteral nutrition; VLBW, Very low birth weight; IUGR, Intra-uterine growth restriction; TOI, Tissue oxygenation index; CSOR, Cerebrosplanchnic oxygenation ratio; CN, Continuous nutrition; BN, Bolus nutrition; NPO, Nothing per os; PSV, Peak sistolic velocity; EDV, End-diastolic velocity; Vmean, Mean velocity; RI, Resistance index; SMA, Superior mesenteric artery.
